# PROTOCOL TITLE

Determination of Dosing and Frequency of BCG Administration Necessary to Alter T-lymphocyte Profiles in Type 1 Diabetes

### SPECIFIC AIMS

Concisely state the objectives of the study and the hypothesis being tested.

To determine whether BCG vaccination can reduce the auto-reactive t-lymphocytes that underlie autoimmunity in the NOD mouse model of Type 1 diabetes and in human Type 1 diabetes. In addition, we will determine whether BCG vaccination increases TNF (tumor necrosis factor, an inflammatory cytokine) levels which underlies the depletion of auto-reactive t-lymphocytes in the NOD mouse. This study is the first step in trying to cure human Type 1 diabetes by altering the underlying autoimmunity.

# BACKGROUND AND SIGNIFICANCE

Provide a brief paragraph summarizing prior experience important for understanding the proposed study and procedures.

Type 1 diabetes is an autoimmune disease mediated by t-lymphocyte destruction of the insulin producing beta-cells of the pancreas. In the NOD mouse model of autoimmune diabetes, which closely resembles human Type 1 diabetes, “poorly educated” auto-reactive t-cells destroy beta-cells. These abnormal lymphocytes (white cells) can be depleted by manipulations that increase TNF. Destroying these abnormal lymphocytes has allowed re-education of the immune system and facilitated beta-cell replacement in the diabetic mice. Moreover, correction of the autoimmunity has resulted in regrowth of islet cells in the pancreas, effectively curing established diabetes in the NOD model of diabetes. If similar results can be obtained in human diabetes, a true cure of this autoimmune disease may be possible. The proposed study is the first step in determining whether manipulations similar to those used in NOD mice are effective in human diabetes.

###### RESEARCH DESIGN AND METHODS

Briefly describe study design and anticipated enrollment, i.e., number of subjects to be enrolled by researchers study-wide and by Partners researchers. Provide a brief summary of the eligibility criteria (for example, age range, gender, medical condition). Include any local site restrictions, for example, “Enrollment at Partners will be limited to adults although the sponsor’s protocol is open to both children and adults.”

In this pilot study, we will randomly assign volunteers with type 1 diabetes to be vaccinated with saline (control group) or with BCG, a bacterial product that has been used to immunize many millions of people against tuberculosis for more than 30 years, to try to deplete the auto-reactive t-lymphocytes in persons with Type 1 diabetes. The BCG will be administered intradermally with the same technique used for vaccination, using the standard vaccination dose. If no untoward side-effects occur, the vaccination will be repeated after a 4 week interval. An increase in TNF levels is the mechanism of auto-reactive t-cell depletion in the NOD mouse model and we will determine whether TNF levels are increased, concurrent with auto-reactive t- lymphocyte depletion, in Type 1 diabetic volunteers after the first and/or second BCG vaccination.

Volunteers, recruited by advertisement or from the MGH Diabetes Clinic, will be asked to come to the Diabetes Research Center. The volunteer will be requested to bring a non-diabetic volunteer. If the type 1 diabetic volunteer cannot identify a non-diabetic volunteer, a separate recruitment will identify such an individual. This non-diabetic subject will provide a blood sample during visits when the diabetic subject has autoreactive T-cells drawn. This will serve as a control sample for the cell-based laboratory analyses. The non-diabetic subject will not have any other interventions. We will recruit volunteers for the study that will be randomized to treatment, placebo or the serially followed reference groups.

Diabetics who are 18 to 55 years old and who have no demonstrable insulin secretion will be eligible. Patients with a history of tuberculosis or a past history of a positive PPD test or previous BCG vaccination, or a history of HIV or chronic skin conditions such as eczema, will be excluded.

The complete Diabetic subject inclusion criteria are:

- Type 1 diabetes treated continuously with insulin from time of diagnosis
- Age 18-55
- Anti-GAD positive
- HIV antibody negative
- Normal CBC
- Negative intermediate PPD test performed and read by study staff
- HCG negative (females)

The complete Diabetic subject exclusion criteria are:

- History of chronic infectious disease, such as HIV
- History of tuberculosis, TB risk factors, or history of + PPD, or BCG vaccination
- Treatment with glucocorticoids (other than intermittent nasal steroids) or disease or condition likely to require steroid therapy
- History of HIV
- Other conditions or treatments associated with increased risk of infections such as patients with a previous history of severe burns, or treatment with immunosuppressive medications of any type (e.g. imuran, methotrexate, cyclosporine, etanercept, infliximab) for any reason
- Current treatment with aspirin > 160 mg/day or chronic, daily NSAIDs
- Fasting or stimulated (1 mg glucagon stimulation test) c-peptide > 0.2 pmol/mL
- History of keloid formation
- HbA1c > 8.0%
- Pregnant or not using acceptable birth control
- Living with someone who is immunosuppressed and/or at high risk for infectious diseases (for example HIV+ or taking immunosuppressive medications for any reason)

Control Non-diabetic Subjects inclusion criteria:

- Age 18-55, no history of autoimmune diseases or diabetes
- No history of HIV
- No history of autoimmune disease or type 1 diabetes (use of insulin continuously since diagnosis) in first degree family members

Briefly describe study procedures. Include any local site restrictions, for example, “Subjects enrolled at Partners will not participate in the pharmacokinetic portion of the study.” Describe study endpoints.

The study will be performed in the outpatient MGH Diabetes Center or in the outpatient General Clinical Research Center. After initial screening, including obtaining baseline blood tests and performing a standard PPD test, diabetic subjects will be randomly assigned to receive either a saline (placebo) or the BCG vaccination. Weekly blood tests will track changes in t-lymphocytes and TNF levels. The BCG vaccination will be repeated 4 weeks after the initial vaccination and will be followed by monitoring for another 16 weeks. Including the screening tests, seventeen visits to the outpatient Diabetes Center or GCRC will be required over the 20-week study. Except for visits three and eight, which will require approximately 3 hours, the visits will take less than 15 minutes.

For studies involving treatment or diagnosis, provide information about standard of care at Partners (e.g., BWH, MGH) and indicate how the study procedures differ from standard care. Provide information on available alternative treatments, procedures, or methods of diagnosis.

STANDARD OF CARE: There is no currently available treatment that can cure or ameliorate the autoimmunity that underlies Type 1 diabetes, once established. Several other currently unapproved, research interventions have been shown to delay the rate of loss of insulin secretion in newly diagnosed patients, but such interventions (e.g. immunosuppressive regimens, autologous bone marrow transplantation) are thought to be ineffective in established diabetes (such as that in the current protocol). Standard therapy of Type 1 diabetes includes use of insulin to achieve glycemic levels as close to the non-diabetic range as possible with the expectation that long-term complications affecting eye, kidney, nerve and cardiovascular system can be reduced, if not eliminated. Such therapy includes frequent (4-6 times per day) monitoring of glucose levels and therapeutic diets. If complications of diabetes develop, they are treated (e.g. laser therapy for eye disease, dialysis or transplantation for end-stage kidney disease). Standard therapy will be continued during this study.

Describe how risks to subjects are minimized, for example, by using procedures which are consistent with sound research design and which do not unnecessarily expose subjects to risk or by using procedures already being performed on the subject for diagnostic or treatment purposes.

MINIMIZATION OF RISK

None of the proposed interventions are routine in the US, although BCG vaccination continues to be used worldwide to protect persons against tuberculosis. Risk from the vaccination, which usually entails the development of an inflammatory papule followed by a scab formation, will be reduced by close, weekly observation of the vaccination site. Any inflammation or scarring more than moderate on an objective scale will result in the repeat vaccination not being given. A small (usually 3-7 mm) scar often develops at the site of vaccination

Describe explicitly the methods for ensuring the safety of subjects. Provide objective criteria for removing a subject from the study, for example, objective criteria for worsening disease/lack of improvement and/or unacceptable adverse events. The inclusion of objective drop criteria is especially important in studies designed with placebo control groups.

ENSURING SUBJECT SAFETY

See minimization of risks above. Any inflammation or scarring associated with the vaccination that is more than moderate on an objective scale will result in the repeat vaccination not being given.

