## MONITORING AND QUALITY ASSURANCE

Describe the plan to be followed by the principal investigator/study staff to monitor and assure the validity and integrity of the data and adherence to the IRB-approved protocol. Specify who will be responsible for monitoring, and the planned frequency of monitoring. For example, specify who will review the accuracy and completeness of case report form entries, source documents, and informed consent.

NOTE: Regardless of monitoring plans by the sponsor or others, the principal investigator is ultimately responsible for ensuring that the study is conducted at his/her investigative site in accordance with the IRB-approved protocol, and applicable regulations and requirements of the IRB.

The PI and study coordinator will be responsible for overseeing the quality assurance regarding the conduct of the study.

Adherence to the protocol, including strict adherence to the eligibility criteria for recruitment, oversight of vaccinations and safety monitoring, and collection of data will be examined on a regular basis, need for corrective actions noted, and follow-up to determine that any identified problems are rectified will be the responsibility of the PI. Any outside (non-MGH) laboratory, including commercial laboratories, will be reviewed to ensure that quality control is at a level that is consistent with clinical research.

The PI will present a summary of the monitoring to the DSMB on a regular basis, and no less frequently than every 6 months.

For guidance, refer to the following Partners policies:

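### The eligibility summary excludes chronic skin conditions such as eczema, but the exclusion list labelled complete does not name them

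*Protocol*

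**What the plan says.** Research Design and Methods of the protocol states eligibility twice for diabetic volunteers.

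The first statement is a short prose summary. After tuberculosis, a positive PPD test and earlier BCG vaccination, it ends: "or a history of HIV or chronic skin conditions such as eczema, will be excluded".

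The second is a pair of bulleted lists, introduced by "The complete Diabetic subject inclusion criteria are" and "The complete Diabetic subject exclusion criteria are". The exclusion list has one item that concerns the skin by name, "History of keloid formation". Two other bullets could reach some people with skin disease indirectly:

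- "Treatment with glucocorticoids (other than intermittent nasal steroids) or disease or condition likely to require steroid therapy"
- "Other conditions or treatments associated with increased risk of infections such as patients with a previous history of severe burns", a bullet that goes on to cover immunosuppressive medication taken for any reason.

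For those who pass screening, the procedures text says "diabetic subjects will be randomly assigned to receive either a saline (placebo) or the BCG vaccination". Under Monitoring and Quality Assurance, the protocol requires "strict adherence to the eligibility criteria for recruitment" and makes the principal investigator responsible for it.

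**The concern.** A summary may leave out items that the full list contains. Here the reverse happens: the summary holds an exclusion that the list lacks, and the list is labelled complete. A reader who takes that label at its word has no reason to go back to the summary for further criteria.

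Two things are at stake. The first is who enters the trial. BCG is given into the skin, and the reactions described under Minimization of Risk and Foreseeable Risks are mainly local: a papule, a scab, a rash that may scale, and often a scar. A skin-related exclusion therefore bears on the trial's most expected safety outcome.

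The second is adherence. With two versions of the criteria, the same enrolled person complies with one and is a deviation under the other, so the promised check of eligibility has no single standard. The study is a small pilot. The planned data and safety review takes place once 6 subject pairs have finished, with 3 diabetics on active vaccine. One vaccinated person of disputed eligibility would be 1 of those 3.

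**Working it through.** No arithmetic underlies this point, and the plan gives no figure to reproduce. The check sets each exclusion named in the summary against the two lists.

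| Exclusion in the summary | Found in the complete lists? |
|---|---|
| Tuberculosis | Yes, exclusion list |
| Positive PPD test | Yes, same exclusion bullet; a negative PPD is also an inclusion criterion |
| Previous BCG vaccination | Yes, same exclusion bullet |
| HIV | Yes, exclusion list; a negative HIV antibody test is also an inclusion criterion |
| Chronic skin conditions such as eczema | No, in neither list |

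Result: 4 of 5 carry over and 1 of 5 does not. The exclusion list has 11 bullets and the inclusion list 7; none of the 18 names eczema or chronic skin conditions. Eczema is mentioned nowhere else in the protocol.

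The next question is whether some other bullet covers the missing item in substance.

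1. **Keloid history.** This is a different condition, so it does not stand in for eczema.
2. **Glucocorticoids.** The bullet removes people treated with glucocorticoids, with nasal use as the only exemption, and people likely to need steroid therapy. Some people with chronic skin disease meet it. Those who neither take nor are likely to need steroids do not.
3. **Infection risk.** The bullet is open-ended and leaves room for judgement. Its condition example is severe burns, so whether eczema counts depends on the screener.
4. **Immunosuppressive medication.** This part of the same bullet removes people treated with such drugs, including for skin disease, but only them.

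A person with a chronic skin condition who falls under none of items 1 to 4, and who otherwise qualifies, passes every listed criterion and fails the summary. The contradiction is confined to that group. Once admitted, such a person is randomised, so vaccination with BCG follows only if that arm is drawn. Non-diabetic controls are not affected, because they give blood samples and receive no vaccination.

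**The case against.** The best defence is that the summary is itself binding text. It stands directly above the lists, says plainly that such patients are excluded, and nothing withdraws it. A careful investigator held to strict adherence would read both and keep these people out. The listed bullets also remove part of the group. All of this is fair. It narrows the consequence, but it does not explain why a list called complete omits one of the summary's exclusions.

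A reader might infer more than the documents support, in four ways:

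- **That screening by the list would vaccinate people meant to be excluded.** Admitted subjects may receive saline, so the list could lead to vaccination but need not.
- **That staff screen from the list alone.** The protocol does not say so. The recruitment and consent sections have a coordinator describe the study and a study physician take consent at a screening visit; neither says which text drives the screening form.
- **That every applicant with a chronic skin condition is eligible under the list.** The steroid, infection-risk and immunosuppressive-medication criteria contradict this. For the same reason an assumed prevalence, say 2% to 10% of applicants (1 in 50 to 1 in 10), would not measure the problem. It counts everyone with skin disease, before those criteria and randomisation are applied.
- **That skin disease would distort the grading that decides on the repeat vaccination.** This is plausible, but the protocol ties the grading to reactions associated with the vaccination. Nothing in it shows that disease elsewhere on the skin would interfere.

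**Conclusion.** The inconsistency is real and survives the objections. One of the five exclusions in the summary is missing from a list that claims to be complete, and no other criterion fully replaces it. The affected group is people with a chronic skin condition who escape the steroid, infection-risk and immunosuppressive-medication criteria. Its size cannot be derived from the protocol, and no figure is offered here.

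The conclusion assumes only that the label complete means what it says and that screening might follow the list. It does not assume that screening would follow the list, and it takes no position on which of the two rules is clinically right. The flaw should be fixed, since it concerns who may receive an intradermal vaccination and a vaccination already given cannot be undone. It is not a flaw in the comparison: no endpoint, group contrast or sample size depends on it.

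**What to change.** Before screening, reconcile the eligibility summary and the diabetic exclusion list so that one list states whether chronic skin conditions are an exclusion, and use that single list on the screening form. If the sponsor still intends the exclusion given in the summary, it must appear in the list labelled complete. If it was dropped on purpose, the summary must be corrected. That choice belongs to the sponsor and the investigator.

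The cost is one line in the protocol and the matching line on the screening form. If the exclusion stays, the recruitment pool may be slightly smaller. No visit, test or procedure is added.

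### Non-diabetic assay controls are not screened for prior BCG, tuberculosis or positive PPD, and only partly for steroid or immunosuppressive treatment, so the reference sample can carry the exposure under study

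*Protocol*

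**What the plan says.** All the relevant text is in the protocol, Research Design and Methods.

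- **Role of the control.** Each diabetic volunteer is asked to bring a non-diabetic, or one is recruited separately. That person gives blood at the visits when the diabetic's autoreactive T cells are drawn: "This will serve as a control sample for the cell-based laboratory analyses". Controls undergo nothing else.
- **Control criteria.** There are three: "Age 18-55, no history of autoimmune diseases or diabetes"; "No history of HIV"; and "No history of autoimmune disease or type 1 diabetes (use of insulin continuously since diagnosis) in first degree family members".
- **Diabetic criteria on the same exposures.** Diabetics are excluded for "History of tuberculosis, TB risk factors, or history of + PPD, or BCG vaccination", for "Treatment with glucocorticoids (other than intermittent nasal steroids) or disease or condition likely to require steroid therapy" and for "treatment with immunosuppressive medications of any type (e.g. imuran, methotrexate, cyclosporine, etanercept, infliximab) for any reason". They must also have "Negative intermediate PPD test performed and read by study staff".
- **Household rule.** A diabetic who lives with someone immunosuppressed, or at high risk of infectious disease, is excluded. Use of immunosuppressive medication by that person is given as an example.

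**The concern.** The trial asks whether BCG raises TNF and depletes autoreactive T cells (Specific Aims). A reference for the T-cell assays should be free of the exposure being tested and of drugs that act on the same pathway. As written, a control may have been vaccinated with BCG, may have had tuberculosis, or may be taking a glucocorticoid or an immunosuppressive drug for a non-autoimmune reason. Two of the drugs named in the diabetic exclusion, etanercept and infliximab, block TNF.

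BCG exposure among controls is not far-fetched on the protocol's own account. Foreseeable Risks and Discomforts describes more than 30 years of use in many countries, Canada and western Europe among them. Controls are companions or advertised volunteers, and no criterion asks where they grew up or whether they were vaccinated.

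What is at stake is how the reference readings can be interpreted. If a diabetic's T-cell profile is judged against a control with an unrecorded exposure, a difference, or the lack of one, cannot be attributed cleanly to diabetes or to treatment. If history is not asked at entry, the exposure may be hard to establish later.

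**Working it through.** The protocol states no figure on this point, so there is nothing to reproduce. The check sets the two eligibility lists side by side and then traces where an exposed control could enter a result.

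**Step 1. The lists compared.**

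| Exposure | Diabetic subjects | Control criteria | Indirect cover for controls |
|---|---|---|---|
| Prior BCG | Excluded | Silent | None |
| Tuberculosis or known positive PPD | Excluded; negative PPD also required | Silent | No rule asks for either history |
| Immunosuppressive or anti-TNF drugs | Excluded | Silent | Partial: autoimmune bar and household rule |
| Glucocorticoids | Excluded, intermittent nasal use aside | Silent | Partial: autoimmune bar; household rule if steroids count as immunosuppressive |
| HIV | Excluded | Excluded | Not needed |

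**Step 2. What the indirect cover reaches.** The autoimmune bar removes people treated for autoimmune disease. The household rule works through the diabetic's eligibility, so it reaches only controls who live with the diabetic. The remaining drug gap is a control who is neither cohabiting nor treated for autoimmune disease, for example a friend or a separately recruited volunteer. The household rule does not ask about past vaccination, past tuberculosis or a known positive skin test, so the BCG and tuberculosis gap stays open.

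**Step 3. Where an exposed control could enter a result.** Let D be a diabetic's reading, C the paired control's reading without exposure, and δ the unknown shift due to the control's exposure. The subscripts 0 and t mark baseline and a later visit.

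- *BCG versus saline, diabetics' readings only:* the contrast uses D alone, so δ does not enter.
- *Diabetics versus reference at one visit:* the comparison is D − (C + δ), so δ enters in full.
- *Change from baseline referenced to the pair:* (Dₜ − Cₜ − δₜ) − (D₀ − C₀ − δ₀) = (Dₜ − D₀) − (Cₜ − C₀) − (δₜ − δ₀). A constant shift, as remote BCG might give, cancels. A shift that varies over time, as with intermittent drug use, does not.
- *Arm contrast of pair-referenced readings at one visit:* δ enters. A control's past exposure does not depend on the diabetic's allocation, provided the control is not chosen in light of it. The expected difference between arms is therefore zero, and what remains is added variance and chance imbalance.

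**Step 4. Size.** A numerical estimate would need the share of exposed controls, the shift δ, the assay standard deviation and the number of pairs. The protocol gives none of these. The 6 pairs in Data and Safety Monitoring, 3 of them with active vaccine, mark a review point and not the study size. Any figure would simply restate the assumptions chosen, so none is given.

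**The case against.** The strongest reply is that the two lists have different purposes. Several diabetic exclusions, such as keloid history and pregnancy, plausibly protect people who receive BCG, and the immunosuppressant item itself is framed around infection risk. Controls receive no vaccine, so asymmetry alone is not an error. That stands, and it limits the point to exposures that could alter a T-cell or TNF readout. For the same reason the aspirin and NSAID limits in the diabetic list need not be copied: nothing in the document ties them to the assays.

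A second reply is that no shift is demonstrated. The control criteria select people without personal or family autoimmunity, who suit a negative reference, and the protocol offers no evidence that remote BCG alters their readings. It also says that BCG is not routinely used in the US (Expected Benefits), which suggests exposure may be uncommon at this centre. This stands too. The point is that the reference can carry the exposure, not that it is shown to do so.

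A reader might go further and infer that unsuitable controls bias BCG versus saline. The document does not support that. The procedures text randomises diabetic subjects to saline or BCG. One looser sentence speaks of randomisation to treatment, placebo or reference groups, but nothing describes readings being divided by, subtracted from or calibrated to those of the paired control. Even if they were, past exposure would be unrelated to allocation.

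**Conclusion.** The point holds in limited form. Controls are not screened for prior BCG, tuberculosis or positive PPD, and are screened only indirectly and in part for glucocorticoid and immunosuppressive or anti-TNF treatment. The sample that serves as control for the T-cell assays can therefore come from someone already exposed to the study agent.

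The consequence is noise or possible contamination in comparisons of diabetics with the reference. Chance imbalance between arms is a further possibility only if results are referenced to the paired control. The randomised comparison remains valid and is not systematically biased.

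This rests on two assumptions: that past BCG or the listed drugs can shift a cell-based readout, which is consistent with the trial's own hypothesis but not shown in the document; and that no further control criteria exist beyond the three listed. The magnitude is unknown. This is a minor point, worth acting on because the remedy is cheap.

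**What to change.** Add to the control non-diabetic criteria in Research Design and Methods, established by history only:

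- no prior BCG vaccination;
- no history of tuberculosis and no known positive PPD;
- no current glucocorticoid treatment, intermittent nasal use excepted, and no current immunosuppressive or anti-TNF treatment.

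No skin test or other procedure is needed, so the statement that controls have no other interventions is unaffected. The cost is a few questions at entry and a slightly smaller pool of eligible controls.

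### No repeat HCG, and no check for newly started steroid or immunosuppressive treatment, is stated before the week-4 BCG dose

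*Protocol*

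**What the plan says.** Three places in the protocol set or restate a condition on the second dose.

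- Research Design and Methods, design paragraph: "If no untoward side-effects occur, the vaccination will be repeated after a 4 week interval".
- Minimization of Risk: "Any inflammation or scarring more than moderate on an objective scale will result in the repeat vaccination not being given".
- Ensuring Subject Safety refers back to Minimization of Risk and repeats the same local-reaction rule.

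The study-procedures paragraph gives the timing with no condition attached: "The BCG vaccination will be repeated 4 weeks after the initial vaccination".

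The criteria on pregnancy and immune status are in the eligibility lists for diabetic subjects. A negative HCG in females is an inclusion criterion. The exclusions include "Pregnant or not using acceptable birth control" and "Treatment with glucocorticoids (other than intermittent nasal steroids) or disease or condition likely to require steroid therapy", as well as any immunosuppressive medication, chronic infection, and living with someone who is immunosuppressed. Screening comes before randomisation.

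After randomisation, the procedures paragraph says: "Weekly blood tests will track changes in t-lymphocytes and TNF levels". Minimization of Risk adds weekly observation of the vaccination site. Monitoring and Quality Assurance makes the principal investigator responsible for adherence to the eligibility criteria at recruitment and for overseeing vaccinations and safety monitoring.

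**The concern.** The trial gives a live vaccine product twice, four weeks apart. By excluding pregnant and immunosuppressed people, the protocol treats those states as reasons not to enter and be vaccinated. If that is the reasoning, it applies equally to the same product at week 4, and any of these states can arise between the doses.

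The two kinds of change differ in how visible they are. Staff seeing a subject weekly may hear about a new course of steroids. An early pregnancy will usually not be seen without a test, and no test is stated after entry.

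The gap also falls where the form asked for explicit content. The prompt for Ensuring Subject Safety requests explicit safety methods and objective criteria for removing a subject. The answer covers local reactions only. Dosing eligibility is a protocol matter, so a statistical analysis plan would not normally supply it.

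What is at stake is chiefly subject safety. New steroid or immunosuppressive treatment could also bear on the T-cell and TNF outcomes. The protocol gives nothing from which to size that effect, and the point does not depend on it.

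**Working it through.** The protocol has no figure of its own to reproduce here. The check is a comparison of what is required at entry with what is stated before dose 2.

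| Item | At entry | Stated before the week-4 dose |
|---|---|---|
| Reaction to dose 1 | not applicable | yes: untoward side-effects; inflammation or scarring worse than moderate |
| HCG (females) | must be negative | none stated |
| Pregnancy, contraception | exclusion | none stated |
| Glucocorticoids, or a condition likely to need them | exclusion | none stated |
| Immunosuppressive medication | exclusion | none stated |
| Chronic infection | exclusion | none stated |
| Immunosuppressed household member | exclusion | none stated |

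**Could a named on-study procedure fill the gap?** The weekly bloods are described for T-lymphocytes and TNF, which do not test for pregnancy. Observation of the vaccination site detects neither pregnancy nor a new drug. Visits three and eight last about 3 hours, but their content is not given.

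**Could the entry list be applied again at week 4?** Not unedited. It contains the exclusion "History of tuberculosis, TB risk factors, or history of + PPD, or BCG vaccination", and every BCG-arm subject has been vaccinated by then. That item obviously refers to vaccination before the study, so it does not show that the other criteria lapse. It does show that some subset would have to apply at re-dosing, and the protocol does not say which.

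**Age of the last stated HCG.** The test is an entry criterion, so it is done no later than dose 1. Dose 2 follows 4 × 7 = 28 days later. The result is therefore at least 28 days old at dose 2.

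**Illustration of size.** The protocol gives no conception rate. Assume that 0.1% to 1% of women using contraception conceive in 28 days. Data and Safety Monitoring refers to 3 diabetics on active vaccine at its first outcome review, and Recruitment Procedures expects about 50% women, so 3 × 0.50 = 1.5 women are expected. The expected number newly pregnant at dose 2 is 1.5 × 0.001 = 0.0015 to 1.5 × 0.01 = 0.015. This counts exposures, not harms, and rests entirely on the assumed range. New steroid or immunosuppressive use cannot be estimated from the document.

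**The case against.** The best case against is that this is silence in a short institutional form. The prompt asks for a brief description of procedures, the answer is a single paragraph, and a recheck at one of the long visits may simply not be written down. The local-reaction rule says when the dose will be withheld and does not claim to be the only reason. Some entry criteria look forward: contraception must be in use, and conditions likely to need steroids are excluded. Subjects are seen weekly, and the investigator oversees vaccinations. The eligibility list also contains items such as an HbA1c limit, so it is not purely a list of vaccine contraindications.

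Much of this stands. An unstated recheck cannot be ruled out, and the safeguards named do lower the chance.

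A reader might infer that, followed as written, the protocol would have a newly pregnant or immunosuppressed subject vaccinated again. The text does not support that. The withholding rule is a sufficient condition, and nothing orders the dose for someone known to be pregnant or immunosuppressed. What the text lacks is a step that would make the state known.

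A reader might also try to size the harm from the severe-reaction frequency in Foreseeable Risks and Discomforts. That is an overall rate per vaccination, reported almost exclusively in immunosuppressed children. It does not measure the extra risk from a missing recheck in adults aged 18 to 55. The protocol likewise states no overall allocation ratio from which to bound the share of subjects affected.

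The objection does not supply any stated means of finding an early pregnancy before dose 2.

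**Conclusion.** The point holds as a minor safety gap. The stated grounds for withholding the second injection cover only reactions to the first. No stated step before week 4 would detect an early pregnancy or require a check for newly started steroid or immunosuppressive treatment.

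The absolute risk is low. The protocol gives no rate for pregnancy between doses, new immunosuppression or fetal harm, so the extra risk cannot be computed from it. The pregnancy part rests on the protocol's own exclusion rather than on a stated harm. The conclusion assumes that the available text describes the procedures fully enough to be followed as a plan. If a recheck is already done, the remedy is only to write it down. It is a cheap improvement.

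**What to change.** Keep the present withholding criteria and add the following under Minimization of Risk and Ensuring Subject Safety:

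> *Before the week-4 injection, HCG is repeated in female subjects and a short checklist is completed. The injection (BCG or saline) is withheld if HCG is positive or the subject newly meets the exclusion for infection, glucocorticoid or immunosuppressive treatment, or an immunosuppressed household member. Subjects not given the second injection remain in scheduled follow-up.*

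The rule is the same in both arms, so withholding does not depend on allocation. The 4-week interval and the 20-week schedule do not change.

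The cost is one HCG per female subject, which can be run on blood already being drawn, and a brief checklist at an existing visit. Rarely, a subject will contribute one dose instead of two.
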